
#### Control group

The participants in this group will receive physiotherapy for 2.5 h/day over 15 consecutive days (the same period as the CIT intervention). The physiotherapist responsible for this group is experienced in stroke rehabilitation and has been working in this area for 10 years.

This conventional training can be defined as intervention without technological resources, using handling, verbal commands, positioning, gait training and/or pre-walking activities such as climbing stairs, balance training, lower limb strengthening, and other exercises that require standing and shifting weight to the impaired side [29].

### Measurements

Patient from both groups will be evaluated at 3 time points: T0 - 1° pre-treatment (1–3 days before the beginning of the protocol), T1 - 2° immediately after the end of the protocol (1–3 days after the last day), and T2 - 3° 6 months after the end of the protocol. All the evaluations will be conducted by an independent, blinded, experienced and trained evaluator (Table 1).

**Table 1 Tab1:** Overview of measurements used in this study

Data	Time
**Demographics**	
Gender, age, time post stroke, type of stroke (ischemic or hemorrhagic), affected side, dominance	T0
**Walking performance measures**	
6min WT	T0, T1, T2
TUG	T0, T1, T2
10mWT	T0, T1, T2
**3-D**	T0, T1
**Balance measure**	
Mini-BESTest	T0, T1, T2
**Self-reported measure**	
LE-MAL	T0, T1, T2

As primary outcomes we have chosen Mini-BESTest and 6min WT, one test for gait performance and one test for balance evaluation.

For the follow-up evaluations, patients will receive, at the end of the protocol, a date to return. Between 30 and 15 days before the date scheduled, we will call them to remember about that. In case of giving up from the protocol we will use all the data collected until the moment of renunciation (it has been predicted at the consent form).

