**Methods:**

The study adopts a randomized, controlled, single-blinded study design. Forty-two patients, who suffered a stroke, who were in the chronic phase of recovery (>6 months), with gait disability (no community gait), and who were able to walk at least 10 m with or without the advice or support of 1 person, will be randomly allocated to 2 groups: the LE-CIT group or the control group (intensive conventional therapy). People will be excluded if they have speech deficits that render them unable to understand and/or answer properly to evaluation scales and exercises selected for the protocol and/or if they have suffered any clinical event between the screening and the beginning of the protocol. Outcome will be assessed at baseline (T0), immediately after the intervention (T1), and after 6 months (T2). The outcome measures chosen for this trial are as follows: 6-min walk test (6minWT), 10-m walk test (10mWT), timed up and go (TUG), 3-D gait analysis (3DGA), Mini Balance Evaluation Systems Test (Mini-BESTest), and as a secondary measure, Lower Extremity Motor Activity Log will be evaluated (LE-MAL). The participants in both groups will receive 15 consecutive days of daily exercise. The participants in the LE-CIT group will be submitted to this protocol 2.5 h/day for 15 consecutive days. It will include (1) intensive supervised training, (2) use of shaping as strategy for motor training, and (3) application of a transfer package (plus 30 min). The control group will receive conventional physiotherapy for 2.5 h/day over 15 consecutive days (the same period as the CIT intervention). Repeated measures analyses will be made to compare differences and define clinically relevant changes between groups.

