#### Data analyses

The software Excel (Microsoft) will be used to tabulate the data and the software SPSS will be used to do the statistical analysis. A significance level of 5% will be adopted.

We will use the Kolmogorov-Smirnov test to analyze the normality of the data. For the characterization of the sample and baseline comparison to test the homogeneity of the sample, the Qui-Quadrado will be used, but if we find statistical differences between the groups we will also analyze the clinical relevance of these differences.

The results will be compared in relation to the type of intervention and at the three timepoints proposed in this study (pre-treatment, post-treatment, and at 6 month follow-up) using the two-way analyses of variance, ANOVA, and the Bonferroni post-hoc test or Friedman, depending on the parameterization of the data.

To analyze the direction and magnitude of outcomes, we will use the Pearson or Spearman test of correlation.

The results will be described with mean and standard deviation for each group and mean and standard deviation of differences between groups and confidence interval.

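### The named three-visit ANOVA or Friedman test cannot, in its standard form, use all data collected before withdrawal: a patient without T2 also leaves the T1 test

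*Protocol article*

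**What the plan says.** **Data rule.** The Measurements section (text after Table 1) covers patients who stop taking part: "In case of giving up from the protocol we will use all the data collected until the moment of renunciation". It adds that the consent form provides for this. The same paragraph plans reminder calls before the follow-up visit, so non-return is anticipated.

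**Analysis.** Data analyses sets out the comparison of the two arms as follows: "at the three timepoints proposed in this study (pre-treatment, post-treatment, and at 6 month follow-up) using the two-way analyses of variance, ANOVA", with Bonferroni post-hoc tests, or Friedman if the data are not suited to a parametric test. On software it says "the software SPSS will be used to do the statistical analysis". The abstract's Methods adds: "Repeated measures analyses will be made to compare differences and define clinically relevant changes between groups". No imputation, mixed model or separate test at T1 is named.

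**What is affected.** The article states: "As primary outcomes we have chosen Mini-BESTest and 6min WT". Table 1 schedules both at T0, T1 and T2, and the last visit is defined as "T2 - 3° 6 months after the end of the protocol". The 3-D gait analysis is scheduled at T0 and T1 only, so a missed T2 does not touch it.

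**Size.** Sample size and justification sets 21 per group, 42 in total, with no stated allowance for loss.

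**The concern.** The article fixes a rule about whose data count and also names a test, and the test in its standard form cannot carry out the rule. Repeated-measures ANOVA in its usual SPSS form works on one row per patient and leaves out any row with a missing visit. Friedman likewise needs complete blocks. A patient who completes the 15 days of treatment, is measured at T0 and T1 and does not come back six months later would therefore be left out of the whole three-visit test, although the T1 value exists.

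The comparison straight after treatment would then rest only on patients who return six months later. That costs precision in a trial of 42. It also conditions the T1 comparison on something that happens after treatment. This is a different problem from patients who stop during training and never have a T1 value.

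The non-parametric branch has a further weakness. Friedman compares visits within one set of patients and has no group factor. If the data send the analysis down that branch, no test of LE-CIT against control is left.

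**Working it through.** **1. The statements side by side.**

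| Pattern of visits | Data rule (Measurements) | Repeated-measures ANOVA, standard form | Friedman |
|---|---|---|---|
| T0, T1, T2 | used | used | used, but no group comparison |
| T0, T1 | T0 and T1 used | patient left out | patient left out |
| T0 only | T0 used | patient left out | patient left out |

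The rule and the named test agree only for patients with all three visits.

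**2. Reproducing the article's own sample size.** Inputs from Sample size and justification: matched-pair t-test, α 0.05 (taken as two-sided), power 0.80 (printed as β), effect sizes 0.93 (Mini-BESTest) and 0.65 (6minWT). Power comes from the noncentral t distribution with n − 1 degrees of freedom and noncentrality d√n.

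- d = 0.93: the smallest n reaching 0.80 is 12 (power 0.834), as stated.
- d = 0.65: the smallest n reaching 0.80 is 21 (power 0.809), as stated.

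**3. Effect of missing T2 values.** The article gives no loss rate, so 10%, 20% and 30% are assumed, equal in both groups and unrelated to outcome. Complete rows per group are 21 × (1 − loss), rounded. The standard error of a difference between two equal groups is proportional to 1/√n, so its ratio to the full-data value is √(21/n). Power uses the formula in step 2 with d = 0.65.

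| Assumed T2 loss | Complete per group | Observed T1 values left out (of 42) | √(21/n) | d√n | 6minWT power, paired formula |
|---|---|---|---|---|---|
| 0% | 21 | 0 | 1.00 | 2.98 | 0.809 |
| 10% | 19 | 4 | 1.05 | 2.83 | 0.764 |
| 20% | 17 | 8 | 1.11 | 2.68 | 0.711 |
| 30% | 15 | 12 | 1.18 | 2.52 | 0.649 |

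By the same formula the Mini-BESTest stays above 0.80 throughout, because 12 per group already gives 0.834. The 6minWT, which sets the trial size, falls below 0.80 at each assumed loss rate.

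**4. Bias.** Under the random loss of step 3 the T1 difference loses precision but stays unbiased. Bias needs return at T2 to depend on gain in a way that shifts the two arms by different amounts. A simulation shows what that could do. It assumed that low gainers in LE-CIT return less often (log-odds 1 per SD of gain), that return is random in control, and correlations of 0.80 (T0–T1), 0.75 (T0–T2) and 0.85 (T1–T2). A true T1 effect of 0.65 SD of change appeared among completers as 0.74, 0.81 and 0.91 at 10%, 20% and 30% loss. With no true effect, the rejection rate at nominal 5% was 5.5%, 7.8% and 10.4%, against 4.6% to 5.2% using all T1 values.

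**The case against.** **Deletion is inferred, not written.** A reader might conclude that the plan prescribes a complete-case analysis or throws the T1 data away. It says neither. Data analyses says two-way ANOVA without the words repeated measures. The abstract says repeated measures without naming ANOVA, and that phrase could cover a mixed model. SPSS also fits mixed models. T1 values from patients without T2 may still enter the means, standard deviations and differences that Data analyses promises to describe. All of this stands, so the point is limited to the named test in its standard form. The alternative reading, an ordinary factorial two-way ANOVA, would keep the T1 rows but treat three measurements on one patient as independent, which is no better.

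**It could be left to an analysis plan.** An unseen document may give an imputation rule or a separate T1 comparison, and that would resolve the conflict. But the article does not simply stay silent: it states a data rule and names methods that do not fit it. It is also possible to read the withdrawal sentence only as consent to keep data. Even so, it says the data will be used, and the named test cannot do that.

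**The size is assumed.** This is correct. No loss rate is stated, and the selection pattern in step 4 is an illustration of what could happen. At 10% loss its effect on the false-positive rate is negligible.

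**A larger power loss might be quoted.** Treating 0.65 as a two-group effect gives power of 54% at 21 per group and 40% at 15. The low starting value comes from the use of a matched-pair formula for a parallel-group trial, which is a separate matter and not a result of missing T2 values.

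**No primary time point is declared.** This is true, and a missing T2 weakens any T2 comparison whatever the method. The avoidable part is the loss of the observed T0 and T1 values.

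**Conclusion.** The point holds in limited form. As named, and with no other method stated, the three-visit test of both primary outcomes excludes a patient who has T0 and T1 but no T2, which does not fit the promise to use everything collected before withdrawal. The Friedman branch additionally provides no comparison of LE-CIT with control.

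At an assumed 10% to 30% missing T2, 4 to 12 of 42 observed T1 values per outcome leave the test. The standard error of the T1 difference rises by 5% to 18%, and 6minWT power by the article's own formula falls from 0.81 to between 0.76 and 0.65.

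A reader might infer that the T1 effect will be biased. The documents do not support that: they give no information on who fails to return, so bias is a possibility under unequal, gain-related loss and not a demonstrated consequence. No figure printed in the article is wrong on this account. The analysis wording should be changed, because the replacement is better and costs almost nothing.

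**What to change.** In Data analyses, replace the ANOVA for each outcome measured at all three visits with a linear mixed model for repeated measures, which SPSS offers:

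- T0, T1 and T2 all as outcomes.
- Visit and group-by-visit effects, with the two groups sharing a common baseline mean (a constrained longitudinal model).
- Unstructured within-patient covariance (six parameters for three visits).
- Every randomised patient with any measurement included. Because T0 is an outcome and not a covariate, patients with T0 only are kept too, as the Measurements section promises.
- The LE-CIT minus control difference with 95% CI reported at T1 and at T2.

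For clearly non-normal data, replace Friedman with a between-group method on change from T0, for example a rank-based or bootstrap comparison at each visit using all available values.

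The cost is analysis wording only: no new patients, visits or data, and the planned 42 is unchanged. As data collection is under way, the change should be dated and recorded before outcomes are examined by group. The small downside is that the model assumes T2 is missing at random given the observed values, which is a weaker assumption than the complete-case test needs.

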Patients will be removed from this trial who (*i*) have two consecutive absences without medical justification and (*ii*) have any clinical intercurrence that makes continuing with the exercises impossible.

Both patient and caregiver will be informed that their participation in this study protocol is totally voluntary and that they are free to discontinue participation at any time. They will also be informed that their treatment and care at AACD will not be affected, regardless of their decision regarding participation in the protocol, but during the 17 days of CIT they cannot enter into another concomitant therapy. The patient will be informed that the recorded data for the final analysis refer to evaluations and treatment applied to this study and that their identity will be always kept confidential. All volunteers will be informed about the potential types of discomfort, the risks, and the procedures employed in the investigation.

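### The data rule for patients who give up does not separate stopping training from withdrawing from assessment, so a consenting patient who stops within the 15 days is left with only a baseline value

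*Protocol article*

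**What the plan says.** All references are to the protocol article.

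- **Measurements, text after Table 1.** The rule is: "In case of giving up from the protocol we will use all the data collected until the moment of renunciation". It adds that the consent form foresees this. The same paragraph says that the return date for follow-up is handed out when the training has ended.
- **Measurements and Table 1.** T0 falls 1–3 days before training and T1 falls 1–3 days after its last day. The third visit is "T2 - 3° 6 months after the end of the protocol". 6minWT and Mini-BESTest, the two primary outcomes, are listed at these three visits only.
- **Population.** Patients are told that "they are free to discontinue participation at any time". The trial also removes those who "have two consecutive absences without medical justification" or who "have any clinical intercurrence that makes continuing with the exercises impossible".
- **Data analyses.** Groups and the three timepoints are compared "using the two-way analyses of variance, ANOVA, and the Bonferroni post-hoc test or Friedman, depending on the parameterization of the data". The Abstract calls these repeated measures analyses.

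**The concern.** A patient can stop the daily sessions and still be willing and able to do a walk test and a balance test. The data rule does not recognise this patient. If the rule is applied to anyone who stops training, the trial loses the post-randomisation outcomes of exactly those who could not or would not complete the course.

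Such losses are unlikely to be random. The section on safety names fatigue and falls as the main risks of the intensity. Only the LE-CIT arm carries homework, a behavioural contract and a further 30 minutes a day on top of 2.5 h of training. Stopping could therefore plausibly differ between arms, although the article gives no rate for either. The comparison would then drift from all randomised patients towards those who tolerated the treatment.

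A second, separate loss may occur at analysis. A patient who attends T1 and misses T2 has a usable T1 value, but a complete-case procedure over three visits would discard it. That would sit badly with the promise to use everything collected.

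**Working it through.** **1. Which primary-outcome values a patient holds, from the visit schedule**

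| Patient leaves | 6minWT and Mini-BESTest values held |
|---|---|
| during the 15 training days | T0 |
| between T1 and T2 | T0 and T1 |

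LE-MAL is administered daily within the LE-CIT package, but it is a secondary measure, and daily use is not described for controls. It does not fill the gap.

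**2. The article's own sample size, to see what loss it allows for**

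Inputs from Sample size and justification: matched-pair t-test, effect size 0.65 for 6minWT and 0.93 for Mini-BESTest, α 0.05, power 0.80. Power comes from the noncentral t with n − 1 degrees of freedom and noncentrality d√n. Two-sided, d = 0.65 gives n = 21 (power 0.809) and d = 0.93 gives n = 12 (power 0.834). Both stated figures reproduce, with no allowance for loss. On that same paired basis, power for 6minWT is 0.764 with 19 patients and 0.711 with 17. Whether a paired basis suits a between-group question is a different matter and is not needed here.

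**3. What a T0-only value contributes to the T1 comparison**

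Assumptions: n = 21 per arm, 4 per arm stop in training (m = 17 complete), unit variance, T0–T1 correlation ρ.

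- *Baseline mean constrained equal between arms.* The variance of the T1 contrast is 2(1 − ρ²)/m. It contains m and not n, so T0-only patients do not enter. At ρ = 0.5 it is 2 × 0.75/17 = 0.0882 with or without them. With all 21 per arm measured at T1 it would be 2 × 0.75/21 = 0.0714.
- *Free baseline means, contrast = difference in change.* Completers only: 4(1 − ρ)/m. With T0-only patients added: 2[(1 − ρ²)/m + (1 − ρ)²/n].
  - ρ = 0.5: 4 × 0.5/17 = 0.1176, falling to 2[0.75/17 + 0.25/21] = 0.1120.
  - ρ = 0.9: 4 × 0.1/17 = 0.0235, falling to 2[0.19/17 + 0.01/21] = 0.0233.

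The gain is nil or very small. The same reasoning holds for T2, with the T0–T2 correlation in place of ρ. In a complete-case ANOVA or Friedman test these patients contribute nothing.

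**4. Missing T2 only**

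If the stated tests are run as standard repeated-measures procedures on complete cases, a patient without T2 is dropped entirely. With an assumed 10–20% missing T2 only, 0.10 × 21 = 2.1 and 0.20 × 21 = 4.2, so about 2–4 patients per arm would lose an observed T1 value.

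**5. Illustration of the bias (gains and counts assumed)**

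Completers in one arm gain 40 m on 6minWT and stoppers gain 0 m.

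| Stoppers of 21 | Mean of all randomised | Overstatement among completers |
|---|---|---|
| 2 | 40 × 19/21 = 36.2 m | 3.8 m |
| 3 | 40 × 18/21 = 34.3 m | 5.7 m |
| 4 | 40 × 17/21 = 32.4 m | 7.6 m |

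This is one arm's mean. For the between-arm difference, add an assumed control gain of 20 m in completers and 0 m in stoppers, with 3 of 21 stopping in each arm. The completers' difference is 40 − 20 = 20 m. The all-randomised difference is (40 − 20) × 18/21 = 17.1 m, so the overstatement is 2.9 m. If instead only the LE-CIT arm loses patients, the full 3.8–7.6 m carries over. The article quotes a clinically important difference of 28–42 m.

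**The case against.** The strongest reply is that the sentence states which data will be used, not that assessment ends when training ends. It refers to the consent form, so it may describe a patient who leaves the study altogether. Ending collection and keeping earlier data is then proper. The word for the protocol does not settle this: Measurements uses it for the training course, Population also uses it for the study. A reader might infer that the plan deliberately stops measuring anyone who stops training. The text does not say so. What stands is that it does not limit the rule to withdrawal of consent either, and nothing provides for the patient in between.

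Three other inferences go further than the article supports.

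- *That an early stopper has no possible T1 or T2 date.* The inclusion criteria book 17 consecutive days with the last for final tests, so a scheduled end can be read. What is missing is a statement that it applies to someone who has stopped.
- *That the analysed set must be completers of all three visits.* No SPSS procedure or complete-case rule is named, and such detail may sit in a statistical analysis plan that is not shown. The loss of T1 values is conditional on a repeated-measures, complete-case reading.
- *That the treatment effect is biased by 4–8 m.* That range describes one arm under assumed gains. Controls also train 2.5 h a day for 15 days, and similar stopping would cancel part of it.

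It is also fair to say that a mixed model does little for T0-only patients, and that changing the data rule alone would clash with the removal rules under Population. Both points stand and shape the fix.

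**Conclusion.** The concern holds in a limited form. As written, stopping training and withdrawing from assessment fall under one rule. A patient who stops within the 15 days and still consents has no provided post-randomisation measurement of either primary outcome. The baseline value left over is worth nothing, or almost nothing, to the T1 or T2 comparison, and no later analysis can recover visits that were not held. This part rests only on the schedule and the wording.

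The loss of T1 values when T2 is missing is conditional on how the ANOVA or Friedman test is run.

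The size cannot be fixed from the article, because no stopping rate is given. Under the stated assumptions, 2–4 stoppers of 21 overstate one arm's 6minWT mean by 3.8–7.6 m. The bias in the between-arm difference depends on how stopping and gains differ by arm and may be smaller. This is a cheap improvement, not a flaw that invalidates the design.

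**What to change.** 1. In Measurements (text after Table 1), state that patients who stop training but still consent to assessment are invited to T1 and T2 on dates fixed by their scheduled course, and that only refusal of assessment ends data collection.
2. Under Population, reconcile the removal wording with this, so that removal for absences or a clinical event does not block T1 and T2 for a patient who still consents. This concerns measurement only and leaves untouched when training stops.
3. In Data analyses, analyse 6minWT and Mini-BESTest by randomised arm with a mixed model for repeated measures, which SPSS offers. It keeps T1 values when T2 is missing. It does not rescue T0-only patients; for them only step 1 helps.

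Cost: protocol and consent wording, a different SPSS procedure, and a few extra visits by the existing evaluator. The estimated effect may turn out smaller, because patients who stopped would be counted.
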